**2.3. BENEFIT / RISK RATIO**
Study risks are low. Electrophysiological tests are routine, non-invasive, and may cause minor discomfort from probe insertion or electrode placement. No additional adverse effects are expected. Participants will not gain direct personal benefit beyond more comprehensive exploration and understanding of their symptoms.

**2.4. EXPECTED OUTCOMES**
This study has several novel aspects:

- Inclusion of rarely studied pauci- or asymptomatic patients
- First study combining three electrophysiological tests typically performed separately
- Potential new insights on test reliability through repeated measures

Patient benefits include:

- Identification of objective markers for symptom impact, enhancing pathophysiological understanding
- Potential future use of these markers to guide therapy
- French validation of Naert et al.’s (2021) questionnaire as a patient-perceived quality-of-care tool

Strategically, this will be the first national multicenter study on SCD, increasing visibility for French otology teams in a field largely dominated by North American research.

**2.5. JUSTIFICATION FOR LOW-INTERVENTION LEVEL**
This study primarily involves non-invasive electrophysiological tests and questionnaires in SCD patients, each taking under 15 minutes. Combining these procedures with quality-of-life questionnaires justifies a category 2 human research study.

**3. RESEARCH OBJECTIVES**

**3.1. PRIMARY OBJECTIVE**
The primary objective of this study is to evaluate the validity of electrocochleography as an objective marker of symptom impact in SCD by examining the association between the elevation of the SP/AP ratio on the side of the SCD and the severity of each cardinal symptom (pulsatile tinnitus, autophony, sound-induced vertigo, pressure-induced vertigo).

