| **PRIMARY OBJECTIVE** | Evaluate EcoG as an objective marker of SSCD symptom severity by studying the association between SP/AP ratio elevation and the severity of each cardinal symptom (pulsatile tinnitus, autophony, sound-induced balance disturbances, pressure-induced balance disturbances). |
| **SECONDARY OBJECTIVES** | Compare associations of SP/AP ratio with symptom severity to associations of VEMP abnormalities, WBT absorbance peaks, and CT-based SSCD characteristics.Assess relationships between anatomical/radiological SSCD features and SP/AP, VEMP, and WBT parameters.Evaluate validity of SP/AP, VEMP, and WBT in relation to quality of life (EQ-5D-5L).Evaluate combined electrophysiological indicators (EcoG ± WBT ± VEMP) for symptom assessment.Assess validity of each individual indicator against Naert symptom severity score (French translation).Identify patient profiles based on vestibular/auditory symptom predominance and objective electrophysiological results.Evaluate reliability of electrophysiological indicators (EcoG, VEMP, WBT) over repeated measures (3 visits, 6 measures) by the same examiner.Validate the French version of Naert’s symptom severity questionnaire. |
| **OUTCOME MEASURES** | **Clinical:** Visual analog scales for each cardinal symptom, Naert questionnaire (French), EQ-5D-5L.**Electrophysiological:** EcoG (SP/AP ratio), VEMP (threshold reduction, abnormally large potentials), WBT (absorbance peak at 1 kHz).**Radiological:** SSCD size, surface, and localization on CT. **Primary endpoint:** Correlation coefficients between SP/AP ratio and symptom severity (visual analog scales) for affected vs. healthy side.**Secondary endpoints:** Correlations between VEMP/WBT/CT abnormalities and symptoms, correlations with quality of life, patient profile identification via PCA and clustering, and reliability/reproducibility assessments using ICC and Bland-Altman methods. |
| **STUDY DESIGN** | Prospective, national, multicenter cohort study of patients with unilateral SSCD confirmed on CT. Descriptive analysis of clinical and paraclinical features and correlations. **Reliability assessment:** 3 visits (<1 month apart), 2 repeated measures per visit, standardized procedures, single trained operator per center. Test-retest reliability of French Naert questionnaire over 3 visits (<3 weeks apart). |

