**4. OUTCOME MEASURES**

This study aims to evaluate the validity of objective para-clinical assessments (electrophysiological and radiological) in measuring the symptom impact of SCD. This objective is based on the correlation of clinical indicators of symptom severity with para-clinical indicators in a construct validation approach according to the hypotheses described in section 2.2, with:

- convergent validity, by verifying positive correlations between symptom impact and electrophysiological or radiological measurements on the pathological side,
- discriminant validity (or divergent validity), by verifying the absence of correlation between symptom impact and electrophysiological or radiological measurements on the healthy side.

All clinical and para-clinical measurements are detailed below, before presenting the validity and reliability outcome criteria for:

- the validity of EcoG and other objective para-clinical assessments (temporal bone CT, PEMV, WBT),
- the reliability of electrophysiological assessments (EcoG, PEMV, WBT),
- the psychometric properties of the Naert questionnaire translated into French.

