**4.2.1.1. ELECTROCOCHLEOGRAPHY**
Two EcoG measurements are performed at each of the three planned visits, recording summation potential (SP) and action potential (AP) at each measurement (see Figure 3). The SP/AP ratio is calculated for each of the 6 measurements, as well as an average SP/AP ratio per visit and an overall average across all 6 measurements.

*Figure 3: Electrode placement and typical EcoG recording (from Interacoustics Academy)*

All recordings are performed by the same examiner within one center using the EcoG module of the Eclipse® modular system by Interacoustics®.

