**4.2.1.3. PEMV**
Two ocular and cervical PEMV recordings are performed at each of the three visits, collecting the PEMV threshold (dB SPL) and wave amplitude characterization relative to the contralateral healthy side (absent, normal, or abnormally large). PEMV thresholds and the proportion of abnormally large PEMV across the 6 measurements are recorded.

All recordings are performed by the same examiner within one center using the EcoG module of the Eclipse® system (Interacoustics®).

In each center, the examiner responsible for electrophysiological assessments will have received standardized training by [name] (Associate Professor, University Clermont-Auvergne, and consultant to Interacoustics®).

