**9.3.2. VISIT PROCEDURE**
The pre-inclusion/inclusion visit is conducted by the investigator. Before any study-related examination, the investigator obtains free, informed, written consent from the participant (or legal representative, if applicable).

At the pre-inclusion visit, the previously performed temporal bone CT will be examined to formally confirm the SCD diagnosis.

At the inclusion visit, the following will be performed:

- Clinical examination and evaluation of cardinal symptoms (pulsatile tinnitus, autophony, sound-induced balance disorders, pressure-induced balance disorders)
- Naert questionnaire
- Electrophysiological measurements recorded twice on the healthy ear and twice on the affected ear:
  - Electrocochleography (EcoG)
  - Ocular and cervical VEMP
  - Wideband tympanometry (WBT)

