**11.2. STATISTICAL METHODS**
Data will be described overall; outliers will be identified and corrected if possible. Missing data will be described for the population.

Inclusion/exclusion criteria, patient follow-up, and reasons for early withdrawal will be described, with a flow chart for inclusions and withdrawals.

Reliability of repeated measures will be evaluated first, as it allows further validity assessment:

- Electrophysiological indicators: intra-patient reproducibility (6 repeated measures), inter-visit (3 visits), intra-visit (2 measures per visit) using Bland-Altman plots (1999) with mean bias, 95% CI, and limits of agreement. Adaptation for more than 2 repeated measures will be used for inter-visit or intra-patient reliability (Jones et al., 2011). Intraclass correlation coefficients with 95% CI will also be calculated.
- The same reliability assessment applies to 3 repeated cardinal symptom measures.

If clinical and paraclinical measures are reliable, the validity of indicators will be analyzed using the mean of 6 repeated electrophysiological measures and the mean of 3 repeated clinical symptom measures.

- Convergent validity: correlations between electrophysiological indicators on the pathological (SCD) side and symptoms (presence, intensity, Naert questionnaire)
- Divergent validity: same analyses for the healthy side
- Correlations between electrophysiological indicators, anatomical-radiological measures, symptoms, and quality of life will be described to better understand construct validity.

If inter-visit reliability does not allow use of repeated-measure means, correlations may be estimated using mixed-effect models after standardization of variables. Psychometric properties of the French-translated Naert questionnaire will be assessed (inter-item correlations, item-total correlations, Cronbach’s alpha). Factor analysis will be performed.

Test-retest reproducibility of the Naert questionnaire will be evaluated by intraclass correlation coefficient and Bland-Altman indicators (3 repeated measures across 3 visits).

Unsupervised multivariate descriptive analysis (PCA, clustering) will define patient profiles based on electrophysiological, anatomical, and symptom characteristics. Supervised modeling (partial least squares regression) may also be applied to predict symptoms from multivariable indicators (+/- anatomical indicators).

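### Healthy-ear SP/AP serves only as a separate no-correlation check; the plan neither adjusts the SCD-side coefficient for it nor compares the two sides directly

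*Protocol*

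**What the plan says.** - **Objective.** Protocol 3.1 aims to study "the association between the elevation of the SP/AP ratio on the side of the SCD and the severity of each cardinal symptom". The analysis sections do not say what elevation is measured against.
- **Derived value.** Section 4.2.1.1 takes the SP/AP ratio of each recording, "as well as an average SP/AP ratio per visit and an overall average across all 6 measurements". No interaural difference or ratio is derived.
- **Convergent analysis.** Section 11.2 specifies "correlations between electrophysiological indicators on the pathological (SCD) side and symptoms", using the mean of the six recordings. There is no healthy-ear term.
- **Healthy ear.** Section 9.3.2 requires "Electrophysiological measurements recorded twice on the healthy ear and twice on the affected ear", and 9.4 and 9.5 repeat this at visits 2 and 3, so each completer has six healthy-ear EcoG readings. Section 4 gives their role: "by verifying the absence of correlation between symptom impact and electrophysiological or radiological measurements on the healthy side". Section 11.2 carries this out: "Divergent validity: same analyses for the healthy side".
- **Summary.** Section 1 words the primary endpoint as "Correlation coefficients between SP/AP ratio and symptom severity (visual analog scales) for affected vs. healthy side". It names both sides but gives no statistic that contrasts them.
- **PEMV.** Section 4.2.1.3 records "wave amplitude characterization relative to the contralateral healthy side (absent, normal, or abnormally large", together with a PEMV threshold in dB SPL that is not referenced to the other ear.

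**The concern.** Part of a patient's SP/AP may be common to both ears, for example through age, general cochlear status or recording conditions. That common part can act in two ways. If it is unrelated to symptoms, it is noise that shrinks the SCD-side correlation. If it is related to symptoms, it produces an SCD-side correlation that has nothing to do with the dehiscence.

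The plan meets the second risk with two separate readings: a significant positive correlation on the SCD side (4.3.1) and no correlation on the healthy side. It has nothing for the first. Two separate readings do not tell whether the sides differ. The pair can be satisfied when both ears are equally related to symptoms, and it can fail when only the SCD ear matters but the ears are correlated. At stake is whether SP/AP is declared a side-specific marker for the right reason.

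**Working it through.** **Inputs.** From the protocol: n = 100 (11.1); Pearson r or standardised regression coefficient (4.3.1); expected healthy-side correlation of zero (4.3.1). Assumed, because the documents do not give it: inter-ear SP/AP correlation ρ of 0.3, 0.5 or 0.7. Also assumed: two-sided 5% tests, with absence of correlation read as a non-significant result. The protocol does not say how absence is to be judged. Write r for the SCD-side and h for the healthy-side correlation with a symptom score.

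**1. The plan's own precision.** The 95% interval is tanh(atanh(r) ± 1.96/√97).
- r = 0.50: 0.337 to 0.634, width 0.2975 (stated: below 0.30).
- r = 0: ±0.196, width 0.393 (stated: below 0.40).

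Both figures reproduce. Even a healthy-side estimate of exactly zero leaves values up to about 0.2 open.

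**2. Power of the healthy-side check.** Power ≈ Φ(atanh(h)·√97 − 1.96).

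| True h | 0.10 | 0.20 | 0.30 | 0.40 |
|---|---|---|---|---|
| Detected | 17% | 52% | 86% | 99% |

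A strong shared factor is usually seen. A weak one is often missed.

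**3. A shared factor that passes the pair of checks.** Simulation at n = 100, trivariate normal data, the same true correlation in both ears.

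| | ρ = 0.3 | ρ = 0.5 | ρ = 0.7 |
|---|---|---|---|
| r = h = 0.20: healthy side non-significant, among significant SCD-side results | 40% | 33% | 25% |
| r = h = 0.30: SCD side significant and healthy side not, among all studies | 10% | 9% | 7% |
| r = h = 0.30: adjusted coefficient significant, among all studies | 64% | 44% | 26% |

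The last row matters for the remedy. With r = h = 0.30 the partial correlation falls only to 0.23, 0.18 or 0.13, not to zero.

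**4. A true SCD-side effect that fails the pair.** If symptoms depend only on the SCD-side level, then h = ρr. For r = 0.50 this gives h = 0.15, 0.25 and 0.35. By the formula in step 2 the healthy side is significant in 32%, 71% and 95% of studies. A null healthy side therefore does not follow from SP/AP being a valid marker once the ears are correlated. The adjusted coefficient stays significant in at least 97% of simulated studies.

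**5. Dilution.** Partial r = (r − hρ)/√((1 − h²)(1 − ρ²)). With h = 0 and r = 0.40:
- ρ = 0.3: 0.40/√0.91 = 0.42
- ρ = 0.5: 0.40/√0.75 = 0.46
- ρ = 0.7: 0.40/√0.51 = 0.56
- ρ = 0: 0.40, no gain

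A plain interaural difference is not a safe substitute. Its correlation is (r − h)/√(2(1 − ρ)). For r = 0.50 and h = 0 this is 0.42 at ρ = 0.3, 0.50 at 0.5 and 0.65 at 0.7, so it loses whenever ρ is below 0.5.

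**6. What a direct comparison would detect.** Steiger's test uses (atanh r − atanh h)·√97/√(2 − 2s), where s is the correlation between the two Fisher z values. For r = 0.50, h = 0.25, ρ = 0.5: s = 0.442, so the expected statistic is (0.549 − 0.255)·9.849/1.056 = 2.74, and power is Φ(2.74 − 1.96) = 78%. When r = h the test rejects at its nominal 5%.

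**The case against.** **The readings are not left out.** A reader might infer that the healthy-ear data are ignored. They are not: 4, 4.3.1 and 11.2 give them a defined role, and the summary's primary endpoint names both sides. This stands, and the point is confined to how they are used.

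**The planned check beats adjustment against a strong shared factor.** With 0.30 in both ears the pair misleads in 10%, 9% or 7% of studies, whereas the adjusted coefficient is still significant in 64%, 44% or 26%. This also stands. A reader might infer that adjusting for the healthy ear removes both dilution and imitation; it does not, and its significance alone must not decide attribution. The defence does not cover a weak shared factor (step 3, first row) or a true effect with correlated ears (step 4).

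**Adjustment changes the question.** Section 3.1 asks about SP/AP on the SCD side, and 2.1.2.3 describes absolute norms for the ratio. The raw coefficient is a legitimate primary quantity, and this is why it should stay.

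**The gain is speculative.** At ρ of 0.3 or 0.5 the shift from 0.40 to 0.42 or 0.46 lies well inside the 95% interval of 0.22 to 0.55. Dilution alone would be a weak reason to act.

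**EcoG is not generally disadvantaged against PEMV.** A reader might infer that every PEMV measure is referenced to the healthy ear while EcoG is not. Only the amplitude grading is. PEMV threshold, WBT and CT size have no contralateral reference either.

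**This could sit in a SAP.** An extra covariate could. But the protocol itself fixes the estimator and the role of the healthy ear, and its summary announces a contrast of sides that no section defines.

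**Conclusion.** The point holds in a limited form. The raw SCD-side correlation is an acceptable primary quantity and the stated precision is correct. What is badly fixed is the inference about side: two separate results stand in for a comparison. At n = 100 this can err in both directions. A weak factor shared by both ears (0.20 each) passes in 25% to 40% of studies with a significant SCD side, and a true SCD-side effect of 0.50 is accompanied by a significant healthy side in 32% to 95%. Dilution is secondary and is nil if the ears are uncorrelated.

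All ranges rest on an assumed inter-ear correlation of 0.3 to 0.7, approximately normal data and 5% tests. The study's own data will supply the inter-ear correlation.

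**What to change.** 1. Keep the raw SCD-side correlation as primary. State in 3.1 what elevation refers to, and bring the endpoint wording in section 1 into line with 3.1.
2. In 4.3.1 and 11.2, report beside each raw coefficient the one adjusted for the patient's mean healthy-side SP/AP, as a partial r or as the standardised regression coefficient that 4.3.1 already admits.
3. Test SCD-side against healthy-side r directly with a test for dependent correlations (Williams or Steiger), and give the difference with its interval. Base any claim of side-specificity on this comparison, not on a non-significant healthy side and not on significance of the adjusted coefficient alone.
4. Do the same for the continuous PEMV threshold and the WBT measures, so that the markers are treated alike.

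**Cost.** No new data and one degree of freedom. If symptoms follow the total SCD-side level (h = ρr), partial r falls somewhat: at r = 0.50 and ρ = 0.5 it is (0.50 − 0.125)/√((1 − 0.0625)(1 − 0.25)) = 0.45. The standardised coefficient is unchanged in that case, which is a reason to report it too.

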**3.2. SECONDARY OBJECTIVES**

- To compare the observed association between the elevation of the SP/AP ratio in electrocochleography and symptom severity with the respective associations observed between PEMV alterations and symptom severity, wideband tympanometry and symptom severity, temporal bone CT and symptom severity (evaluated for each cardinal symptom).
- To evaluate the associations between the anatomical-radiological characteristics of SCD (size, location) on temporal bone CT and:
  - the elevation of the SP/AP ratio in electrocochleography,
  - PEMV alterations (lowered PEMV threshold, abnormally large PEMV),
  - and changes in the absorbance peak in wideband tympanometry.
- To assess the validity of SP/AP ratio elevation in electrocochleography, PEMV threshold lowering, and absorbance peak changes in wideband tympanometry, on the SCD side, in relation to quality of life as measured by a generic questionnaire (Euro-QoL 5D).
- To evaluate the validity of combined electrophysiological indicators (EcoG +/- WBT +/- PEMV) in assessing the symptom impact of SCD.
- To evaluate the validity of each indicator (SP/AP ratio in EcoG, PEMV threshold lowering, absorbance peak changes in WBT, and anatomical-radiological characteristics of SCD) by studying their association with symptom severity scores measured using the French translation of the Naert et al. questionnaire.
- To identify multiple patient profiles according to the coexistence or predominance of vestibular and auditory symptoms, and the results of objective electrophysiological tests (PEMV, WBT, EcoG).
- To evaluate the reliability of these electrophysiological indicators by repeating their measurement by the same examiner:
  - over 3 successive visits (in a clinically stable diagnostic and follow-up context, with no therapeutic intervention between visits) in an outpatient setting within a 1-month interval, allowing assessment of inter-visit reliability,
  - with 2 measurements performed at each of the 3 visits by the same examiner, allowing assessment of intra-visit reliability.
    More broadly, these 6 measurements will be used to assess intra-patient reliability.
- To validate the Naert et al. (2021) symptom severity questionnaire in French.

**4. OUTCOME MEASURES**

This study aims to evaluate the validity of objective para-clinical assessments (electrophysiological and radiological) in measuring the symptom impact of SCD. This objective is based on the correlation of clinical indicators of symptom severity with para-clinical indicators in a construct validation approach according to the hypotheses described in section 2.2, with:

- convergent validity, by verifying positive correlations between symptom impact and electrophysiological or radiological measurements on the pathological side,
- discriminant validity (or divergent validity), by verifying the absence of correlation between symptom impact and electrophysiological or radiological measurements on the healthy side.

All clinical and para-clinical measurements are detailed below, before presenting the validity and reliability outcome criteria for:

- the validity of EcoG and other objective para-clinical assessments (temporal bone CT, PEMV, WBT),
- the reliability of electrophysiological assessments (EcoG, PEMV, WBT),
- the psychometric properties of the Naert questionnaire translated into French.

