**4.3. OUTCOME MEASURES: VALIDITY AND RELIABILITY INDICATORS**

**4.3.1. VALIDITY**
Main indicators for evaluating convergent and discriminant validity of electrophysiological or radiological parameters relative to clinical parameters will be Pearson correlation coefficients (or standardized regression coefficients). According to the pathophysiological hypotheses in section 2.2, we expect:

- Significant positive correlation between the SP/AP ratio in EcoG and severity of each cardinal symptom measured on the corresponding VAS.
- Higher correlation between the pathological-side SP/AP ratio and each cardinal symptom than between SCD anatomical size and surface, proportion of 1 kHz absorbance peaks in WBT, or PEMV alteration and symptom severity measured on the corresponding VAS.
- No correlation between cardinal symptom severity and electrophysiological (or radiological) indicators on the healthy side.
- Moderate correlation between anatomical SCD measurements on CT and PEMV alteration or WBT 1 kHz absorbance peak presence.

Correlation coefficients will also be calculated between combined electrophysiological criteria (EcoG +/- WBT +/- PEMV) and each cardinal symptom severity, between electrophysiological criteria and generic quality of life (EQ-5D-5L), and between electrophysiological criteria and symptom severity on the French Naert questionnaire.

Patient profiles with unilateral SCD will be determined using principal component analysis, supplemented by supervised modeling.

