**11. STATISTICAL ASPECTS**

**11.1. SAMPLE SIZE CALCULATION**
To evaluate reliability and validity of electrophysiological indicators, the sample size was defined to estimate reliability and validity parameters with sufficient precision.

100 patients with 6 repeated measurements will allow estimation of an intraclass correlation coefficient (ICC) > 0.80 with 95% CI width < 0.10.

Additionally, 100 patients allow the following precision for correlation values:

- 95% CI width < 0.30 for Pearson correlation ≥ 0.50
- 95% CI width < 0.40 for Pearson correlation = 0

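### Divergent validity is to be shown by an absent healthy-side correlation, which 100 patients cannot verify, and the difference between the two sides is never estimated

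*Protocol*

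**What the plan says.** Section 4 sets up a two-part construct validation. Convergent validity is shown "by verifying positive correlations between symptom impact and electrophysiological or radiological measurements on the pathological side", and discriminant (divergent) validity "by verifying the absence of correlation between symptom impact and electrophysiological or radiological measurements on the healthy side".

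Section 4.3.1 turns this into expected findings. For EcoG it expects: "Significant positive correlation between the SP/AP ratio in EcoG and severity of each cardinal symptom measured on the corresponding VAS". For the other ear it expects: "No correlation between cardinal symptom severity and electrophysiological (or radiological) indicators on the healthy side".

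Section 11.2 gives the analysis in one line: "Divergent validity: same analyses for the healthy side". Section 11.1 justifies n = 100 by the precision of single correlations, including "95% CI width < 0.40 for Pearson correlation = 0".

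The sections differ on whether the healthy side belongs to the primary endpoint. The research summary (section 1) gives that endpoint as "Correlation coefficients between SP/AP ratio and symptom severity (visual analog scales) for affected vs. healthy side". Section 3.1 frames the primary objective as "examining the association between the elevation of the SP/AP ratio on the side of the SCD and the severity of each cardinal symptom". The primary outcome in the Abstract does not mention the healthy side either.

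**The concern.** The healthy side is the protocol's check that SP/AP reflects the dehiscent ear and not a trait of the patient. As written, the check compares two separate verdicts: a correlation on one side and none on the other. This has three weaknesses.

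- Failing to find a correlation does not verify that there is none. The protocol gives no margin below which a correlation would count as absent.
- One verdict present and the other absent does not show that the two correlations differ. Their difference is not estimated anywhere.
- Sections 9.3.2, 9.4 and 9.5 record both ears of every patient, while each symptom has a single VAS score per patient. If the SCD-side ratio drives the symptom and the two ears' ratios are correlated, the healthy side correlates with the symptom without playing any causal part.

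The divergent verdict could therefore be wrong in either direction. A valid side-specific marker may appear to fail, and a weak marker with no side-specificity may appear to pass.

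**Working it through.** **Inputs from the protocol.** n = 100 (sections 1 and 11.1); 95% CI width below 0.30 for r ≥ 0.50 and below 0.40 for r = 0 (section 11.1); both ears measured in each patient (sections 9.3.2 to 9.5).

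**Assumptions, because the protocol gives no values.** Two-sided 5% level; inter-ear SP/AP correlation ρ from 0 to 0.6; SCD-side r = 0.50, the planning value in section 11.1; normal data. Absence is read as non-significance.

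**1. The plan's own precision.** Fisher interval: tanh(atanh(r) ± 1.96/√97).

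- r = 0.50: 0.337 to 0.634, width 0.2975, which agrees with < 0.30.
- r = 0: −0.196 to 0.196, width 0.393, which agrees with < 0.40.

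The figures in section 11.1 are correct. They also show that an observed healthy-side r of exactly 0 leaves true values up to about ±0.20 open. An observed r of 0.10 gives −0.10 to 0.29.

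**2. Healthy-side correlation induced by a valid marker.** If the SCD side drives the symptom with correlation r, and the healthy ear is related to the symptom only through the SCD ear, then r(healthy) = r × ρ. With r = 0.50 and ρ = 0.4, 0.5, 0.6 this gives 0.20, 0.25, 0.30. The partial correlation of the healthy side given the SCD side is then zero.

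**3. Chance that the healthy side is significant.** The critical value is |r| > 0.197. Analytic check at r = 0.20: atanh(0.20) × √97 = 0.2027 × 9.849 = 2.00, so P(Z > 1.96 − 2.00) ≈ 0.52. The table comes from simulated trivariate-normal trials of n = 100. *Pattern* means SCD side significantly positive and healthy side not significant. *Direct test* is Williams' t for two dependent correlations sharing one variable, upper tail 2.5%:

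T = (a − h)·√{(n−1)(1+c) / [2·((n−1)/(n−3))·D + ((a+h)/2)²·(1−c)³]}, with D = 1 − a² − h² − c² + 2ahc and n − 3 degrees of freedom. Here a, h and c are the sample SCD-side, healthy-side and inter-ear correlations.

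| ρ | true r(healthy) | healthy side significant | pattern seen | direct test detects gap | 95% CI width of difference |
|---|---|---|---|---|---|
| 0 | 0 | 5% | 95% | 97% | 0.50 |
| 0.1 | 0.05 | 8% | 92% | 96% | 0.48 |
| 0.2 | 0.10 | 17% | 83% | 94% | 0.45 |
| 0.3 | 0.15 | 32% | 68% | 91% | 0.42 |
| 0.4 | 0.20 | 52% | 48% | 86% | 0.39 |
| 0.5 | 0.25 | 71% | 29% | 80% | 0.36 |
| 0.6 | 0.30 | 86% | 14% | 71% | 0.32 |

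The width is 2 × 1.96 × the SD of the simulated difference. For example, at ρ = 0.6, 3.92 × 0.081 = 0.32.

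**4. A marker with no side-specificity** (equal true r on both sides, ρ = 0.5). The pattern appears in 17% of trials at r = 0.20, 9% at 0.30, 1% at 0.40 and almost never at 0.50. The direct test gives a false positive in about 2.5% throughout.

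**5. Could absence be shown with a margin?** Two one-sided 5% tests with a true healthy-side r of 0 succeed in about 28% of trials for a margin of ±0.20 and 84% for ±0.30. These margins are illustrative; the protocol has none.

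**The case against.** The strongest defence is that the protocol sets no pass/fail rule. Section 4.3.1 lists expectations, section 5.1 speaks of estimating associations, and section 11.1 plans for precision with no alpha. The word significant is attached only to the SCD side. This stands: treating absence as 5% non-significance is an inference, and the percentages for the pattern depend on it. It does not remove the difficulty. Section 4 still says that absence will be verified, and with no margin the protocol has no valid way to do so.

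A second objection is that the inter-ear correlation is unknown and could be low in unilateral disease. This also stands. Below about 0.4 a valid marker shows the expected pattern more often than not, and at 0 it does so in 95% of trials per symptom.

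Third, section 2.2 hypothesises a strong association, and at r = 0.50 on both sides a non-specific marker almost never shows the pattern. This is correct. The false-pass problem is confined to weak correlations, and from about 0.40 upward the pattern passes a non-specific marker less often than the direct test does.

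Fourth, a difference above zero is not the same as absence: 0.50 against 0.30 would qualify. This is fair, and is why the healthy-side correlation should be reported beside the difference.

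A reader might also infer from the research summary that the primary endpoint is itself an affected-versus-healthy contrast, so that the primary analysis is unsound. The documents do not support this. That wording occurs only in the summary and can mean correlations reported for each side. Section 3.1 confines the objective to the SCD side, and the Abstract's primary outcome has no healthy-side element.

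**Conclusion.** The concern holds for the divergent-validity component and should be fixed. Two parts need no assumption about the data's true values: at n = 100 absence of correlation cannot be verified (about ±0.20 even at an observed r of 0), and the planned analysis never estimates the difference between sides.

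The size of the resulting error depends on assumptions. With SCD-side r = 0.50 and a 5% reading of absence, a valid marker fails the healthy-side check in 5% to 86% of trials per symptom as the inter-ear correlation runs from 0 to 0.6, passing one half at about 0.4. The direct test of the difference succeeds more often than the two-verdict pattern at every value tried. A weak non-specific marker (r = 0.20 on both sides, inter-ear 0.5) shows the pattern in about 17% of trials, against about 2.5% for the direct test.

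It would go too far to say that a valid marker is generally likely to fail, because the documents give no inter-ear correlation. The sample size and the SCD-side primary correlation are not called into question.

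**What to change.** - **Sections 4, 4.3.1 and 11.2.** For each cardinal symptom, report r(SCD side) minus r(healthy side) with a 95% CI for dependent overlapping correlations (Williams/Steiger or a bootstrap resampling patients). Make this the evidence of side-specificity, supported when the interval lies above 0.
- **Same sections.** Report the healthy-side correlation, and its partial correlation given the SCD side, each with a 95% CI, and state what size of correlation the interval excludes. Make no claim of absence from non-significance. If such a claim is wanted, set a margin in advance and state the power for it.
- **Section 11.1.** Add the precision of the difference: 95% CI width about 0.32 to 0.50 at n = 100 for inter-ear correlations from 0.6 down to 0, with SCD-side r = 0.50.
- **Section 1.** Reconcile the affected-versus-healthy wording of the primary endpoint with section 3.1 and the Abstract, so that it is clear whether the healthy side is part of the primary endpoint.

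The cost is a wording change and a few lines of analysis code. Both ears are already measured at every visit, so no new data or patients are needed. The divergent claim becomes less absolute.
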